### Participants

All HICBT therapists employed by participating TTad services will be invited to attend the training and participate in the research.

### The intervention

The 1-day workshop has three main themes: (1) psychoeducation about personality difficulties; (2) building skills, knowledge, and motivation to better meet the needs of clients with personality difficulties when delivering a CBT protocol for anxiety or depression; and (3) highlighting the importance of, and considering how to build, therapist self-care and resilience when working with more complex clients. The content of the workshop is informed by the CBT evidence base, including guidance about how to adapt CBT for complex cases [24, 25] and for personality disorders [26, 27]. The intention is to make ‘explicit’ what is often ‘implicit’ good practice in how TTad therapists are supporting this client group in a way that supports fidelity to the CBT treatment protocol rather than leading to unhelpful therapist drift.

The training is delivered by two experienced CBT trainers (online or face-to-face) and is a combination of didactic teaching, small group exercises, role play illustration, and role play practice of the techniques; in line with the declarative-procedural-reflective (DPR) model of therapist knowledge acquisition and the COM-B model of behaviour change [28, 29]. A detailed logic model of change underpinning the training (developed retrospectively) is included in Additional file 1: Appendix 1.

The objectives of theme 1 are to build therapist knowledge and understanding about the dimensional framework for personality disorders proposed in ICD-11 [7, 8, 30]; to better understand how these features relate to therapy outcomes; to reduce stigma and ambivalence to working with these clients; and to build skills to assess current severity accordingly of these features to inform if a client is likely to benefit from therapy in a TTad service. Updates to clinical guidance are also covered, highlighting that individuals with comorbid formal personality disorder diagnoses should not routinely be denied access to treatments for depression/anxiety [15], although those with more severe presentations may be more appropriately managed in secondary care services like community mental health teams or specialist personality disorder teams rather than in primary care TTad settings.

Theme 2 aims to build therapist knowledge, skill, and motivation (including confidence) to deliver CBT to clients with personality difficulties alongside their depression/anxiety in a way that meets their needs but remains adherent to core CBT principles. The ground covered draws on both guidance and research evidence and includes managing the therapeutic alliance in clients who may have an ambivalent relationship to help (c.f. [24, 31–33]); how to structure sessions with clients who may present in a ‘stably unstable’ fashion [27]; how to formulate interpersonal difficulties in CBT terms [26, 27, 33]; how to help clients build skills in managing emotions and being interpersonally effective (c.f. [34–40]); how to help clients notice strengths and moments of resilience; and how to manage ruptures and risk in sessions (e.g. [26, 27]). The focus is on supporting therapists to ‘do CBT basics well’ in a way that would result in high scores in competence assessment of a depression or anxiety protocol.

Theme 3 runs throughout the workshop, aiming to validate the therapist’s experience of working with complex clients in a pressured TTad context and supporting therapists to manage their own self-care and resilience.

The workshop has been developed by BD from teaching originally delivered as part of core clinical training for HICBT therapists, aiming to support therapists to transition from ‘university’ practice to ‘real world’ practice by teaching key skills in finding flexibility within treatment protocols while maintaining fidelity to the model to meet the needs of more complex TTad clients. Due to the demand from TTad services for training workshops focused on personality difficulties, this training intervention was developed with this specific client group in mind. Refinement of the training over time has included drawing upon feedback from co-facilitators (experienced CBT therapists and trainers), delegate feedback, updates to clinical guidance (e.g. [8, 15]) and research findings (e.g. [4, 5, 9, 11, 13, 14, 34–40]), and expertise from individuals with lived experience and other stakeholders, including clinicians and service leads. The current version of the workshop has been delivered as a routine CPD workshop in three large TTad services, and a single-site pilot study is currently underway. However, an adequately powered evaluation of therapist outcomes such as the present protocol describes has not yet been undertaken.

### Outcomes

We will collect a range of therapist and clinical outcome measurements to address our primary and secondary research aims (See Table 1). Our primary acceptability and feasibility outcomes relating to methodological and procedural uncertainties are described in Table 2, alongside continuation rules to be met in order to progress to definitive trial evaluation. If these rules are not met, it will be assessed whether the project is still viable if modifications are made or whether to stop the project.

**Table 1 Tab1:** Therapist participant and secondary clinical data outcome measurements by time point

Outcome	Measure	Time point
**Therapist participant outcomes**		
** Demographics**	Gender, ethnicity, age group, experience level	Pre-training
** Attitudes**	Bespoke attitudinal questionnaire capturing therapist-perceived confidence and competence in working with clients with personality difficulties (for example, ‘I feel confident recognising, assessing, and deciding whether to take on clients with personality difficulties’) on 5 items (see Additional file 2: Appendix 2). Participants will be asked to judge to what extent the statement is true of them on a 5-point Likert scale from strongly disagree to strongly agree. There are no standard measures fit for purpose (to capture attitude and confidence towards working with individuals with personality difficulties). This novel measure has been piloted in previous workshops for TTad HICBT therapists.	Pre-training; Post-training; 3-month follow-up
** Quantitative workshop feedback**	Therapists will answer a series of 4 questions about the delivery and content of the workshop (for example, ‘I found the workshop theoretically interesting’), rated on a 5-point Likert scale from ‘Strongly disagree’ to ‘Strongly agree’ (Additional file 3: Appendix 3). This 4-item questionnaire captures perceived theoretical interest, usefulness and presentation quality and acceptability of the training; and whether they would recommend to other therapists. There is no standard measure fit for this purpose; however, this bespoke scale has been piloted to capture feedback on previous workshops for TTad HICBT therapists.	Post-training
** Qualitative workshop feedback**	Written qualitative questions capturing therapist feedback on training	Post-training
** Wellbeing**	Therapist wellbeing will be assessed using the (adjusted) Short Warwick-Edinburgh Mental Wellbeing Scale (SWEMWBS) [41] 7-item (self-report measure capturing positive wellbeing experiences (for example, ‘I’ve been feeling optimistic about the future’). Therapists will rate the frequency of positive experiences on a 5-point Likert scale from ‘None of the time’ to ‘All of the time’. This version of the scale is adjusted to capture experiences over the past two weeks (adjusted from past week). This measure has previously been used to assess workforce wellbeing [42].	Pre-training; 3-month follow-up
** Impact of training**	Written qualitative questions capturing therapist experiences of training impacts	Post-training; 3-month follow-up
** Burnout**	Sussex Burnout Scale (SBS) [43]—a 3-item self-report measure of frequency of symptoms of burnout at work (for example, ‘I have little or no energy at work or feel exhausted by my job’). Participants will rate frequency of symptoms over the past month on a 5-point Likert scale from ‘Rarely/Never’ to ‘Everyday/Almost every day’ over the past month.	Pre-training; 3-month follow-up
** Presenteeism and absenteeism**	Therapist presenteeism/absenteeism—presenteeism and absenteeism questionnaire (Additional file 4: Appendix 4)—4-item self-report measure capturing frequency of presenteeism and absenteeism from work (for example, ‘At work I have been bothered by physical or psychological problems’). Participants will be asked to rate the frequency of these experiences over the past month from ‘Not at all’ to ‘Nearly every day’. This novel measure will be used as there are no standard measures available fit for the purpose (brief, self-reported measure).	Pre-training; 3-month follow-up
**Routine clinical outcomes on clients with personality difficulties (measured in 6 m before and after the workshop)**		
** Depression symptoms**	Patient Health Questionnaire (PHQ-9 [44];)—a 9-item self-report measure of frequency of depression symptoms (for example, ‘Little interest or pleasure in doing things’). Respondents are asked to rate frequency of symptoms over the past 2 weeks on a 4-point Likert scale from ‘Not at all’ to ‘Nearly every day’. This scale is validated for use in adolescents and adults.	First and last session
** Anxiety symptoms**	The Generalised Anxiety Disorder scale (GAD-7; [45])—a 7-item measure of anxiety symptom (for example, ‘Feeling nervous, anxious or on edge’) frequency over the past 2 weeks, scored on a 4-point Likert scale from ‘Not at all’ to ‘Nearly every day’.	First and last session
** Work and social functioning**	Work and Social Adjustment Scale (WSAS; [46])—a 5-item measure of impairment in daily functioning (for example, ‘Because of my [problem] me ability to work is impaired’) rated on a 9-point Likert scale from ‘Not at all’ to ‘Very severely’.	First and last session
** Measure of personality difficulties**	Standardised Assessment of Personality: Abbreviated Scale—Self Report version (SAPAS-SR; [47, 48])—8-item binary response (yes/no) measure of personality difficulties (for example, ‘In general, do you have difficulty making and keeping friends. This scale is adapted for use as a self-report questionnaire and respondents are asked to indicate ‘Yes’ when the experience applies to them ‘most of the time in most situations’. This scale has been widely used for rapid screening for personality difficulties within the TTad setting for research purposes and has been adopted into routine practice in some services [4, 5, 9].	First session /instance
** Qualitative experiences of treatment**	Patient Experience Questionnaires	Treatment end

**Table 2 Tab2:** Feasibility and acceptability data, method of measurement, and continuation rule to proceed to randomised evaluation without modification

Feasibility/acceptability outcome	Measurement	Continuation rule
**Recruitment**	*Quantitative data*	
	Number of TTad sites recruited to the research project	≥ 3 IAPT sites recruited
	Percentage of eligible therapists attending the training at each site	≥ 60% attendance
	Percentage of attending therapists completing pre- and post-training surveys	≥ 80% data availability
	Percentage of attending therapists completing 3-month follow-up surveys	≥ 60% data availability
**Acceptability**	*Quantitative data*	
	Feedback data on training (that that the training was theoretically interesting, clinically useful, well presented, and would recommend to other HICBT therapists)	60% agree or strongly agree with each item
	*Qualitative data*	
	Written feedback from therapists on the value of training	No significant concerns emerge about training that cannot be resolved
	Qualitative interviews with therapists	No significant concerns emerge about training that cannot be resolved
	Reporting/identification of serious concerns about the acceptability and feasibility of training by key stakeholders	No serious concerns emerge about training that cannot be resolved
	Reporting/identification of serious negative consequences for therapist participants or the clients they subsequently work with as a result of the training (unexpected, clearly research- or training intervention-related serious adverse reactions).	No serious consequences raised
**Clinical outcome data completion**	*Quantitative data*	
	Percentage of TTad clients receiving routine care during the study with sufficient data for inclusion in secondary analyses (at least one measure of SAPAS-SR personality difficulties and at least × 2 measures of the TTad service minimum dataset [PHQ-9, GAD-7 and WSAS])	≥ 60% data availability
**Proof-of-concept**	*Quantitative data*	
	Therapist attitudinal change in confidence to recognise, assess and triage clients with personality difficulties; to adapt key skills for working therapeutically with this group; and in positivity towards working with this group after completing the training in each service.	Significant improvement from pre to post in all 5 attitudinal domains

In addition to these measures, we will capture clinical data to enable us to generate metrics of engagement including discharge code and number of sessions marked ‘Attended’, ‘Did Not Attend’, and ‘Patient Cancelled’. In line with standard reporting of TTad outcomes, we will also compute the following metrics from clinical outcomes: (i) ‘Recovery’—as defined by moving ≥ 10 to ≤ 9 on the PHQ-9 and from ≥ 8 to ≤ 7 on the GAD-7; (ii) ‘Reliable Improvement’—as defined by improving by ≥ 6 points on the PHQ-9 or ≥ 4 points on the GAD-7; and (iii) ‘Reliable Recovery’—as defined by fulfilling criteria for both ‘recovery’ and ‘reliable improvement’ [49].

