### Study setting

We will purposefully recruit at least three TTad services, chosen to reflect diversity in terms of urban/rural context, levels of deprivation, and ethnicity. Services willing to screen for personality difficulties as part of routine assessment will be eligible to participate as a research site.

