### Statistical methods

#### Primary analyses

Primary analyses will address the acceptability and feasibility aims of the study. We will describe the number of UK TTad services recruited to the study, the number (%) of total eligible therapists identified that attend the training in each site, and the number (%) of attending therapists that complete pre-post follow-up surveys. To determine post-intervention views on acceptability, participants’ mean (SD) ratings of intervention theoretical interest, clinical utility, whether it was well presented, and whether they would recommend to other HICBT therapists were rated on a 5-point Likert scale (See Table 1).

We will report the number (%) of cases included in the secondary data extraction with sufficient data for inclusion within the clinical outcome evaluation.

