#### Secondary analyses

Secondary analyses of therapist outcomes will focus on both therapist outcomes, including proof-of-concept in attitudinal change, wellbeing, and burnout measures and preliminary proof-of-concept that training has the potential to lead to improvements in clinical outcomes for those with personality difficulties.

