#### Clinical outcomes

We will report descriptive statistics (means, standard deviations) to describe the clinical measures and client characteristics at intake within the pre- and post-training intervention cohorts (those engaging in treatment in the 6 months pre- compared to 6 months post-therapist training). This will include PHQ-9, GAD-7, and WSAS mean scores; the proportion of clients showing mild, moderate, and severe cut-offs on each scale; and the proportion of clients scoring 3 or more on the SAPAS-SR (indicative of personality difficulties).

This research is a multi-site observational study prior to conducting a definitive evaluation with a randomised trial and therefore has not been a priori powered to inferentially examine between cohort differences in clinical outcomes. However, it is both possible and useful to estimate the between-cohort effect size (and their 95% confidence interval) on client outcomes to help inform decisions to continue to a definitive evaluation of the training intervention and to inform future power calculations. We will therefore report the observed effect sizes but not *p* values. These analyses will focus solely on the subgroup of participants meeting the criteria for probable personality disorder (3 or more on the SAPAS-SR), which we estimate from previous research to be between 69 and 81% of client treatments [5, 9]. A series of linear regressions will examine whether treatment-cohort (treated before or after training) predicts the number of treatment sessions attended and post-treatment levels of depression (PHQ-9), anxiety (GAD-7), and functioning (WSAS). All analyses will include the training site as a covariate. The post-treatment analyses will adjust for the pre-treatment level of the relevant variable. Comparable binary logistic regressions will examine binary outcomes (rates of reliable improvement, recovery, and reliable recovery; rates of clients with planned discharges), again seeing if the treatment cohort (before or after training) predicts each variable and covarying for the training site. As we do not anticipate sufficient statistical power to do inferential statistics, we will examine the distribution of effect sizes, potentially using confidence intervals and Bayesian methods relative to estimates of minimum clinically important difference on clinical outcomes (cf., [55–58]). All quantitative analyses will take place in SPSS or R.

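### The two-score inclusion rule, read as written, also governs sessions attended and planned discharge, so clients who leave before a second score drop out of two engagement outcomes that need no second score

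*Protocol article*

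**What the plan says.** Table 2 (clinical outcome data completion) sets a continuation rule of at least 60% on this quantity: "Percentage of TTad clients receiving routine care during the study with sufficient data for inclusion in secondary analyses". Sufficient data means "at least one measure of SAPAS-SR personality difficulties and at least × 2 measures of the TTad service minimum dataset", the dataset being PHQ-9, GAD-7 and WSAS. Primary analyses, under Statistical methods, ties the same count to the client evaluation: it will report the cases "with sufficient data for inclusion within the clinical outcome evaluation". Secondary analyses describes that evaluation as "preliminary proof-of-concept that training has the potential to lead to improvements in clinical outcomes for those with personality difficulties".

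Clinical outcomes then lists the cohort regressions. Linear models examine whether cohort "predicts the number of treatment sessions attended and post-treatment levels of depression (PHQ-9), anxiety (GAD-7), and functioning (WSAS", with sessions attended in the same sentence as the symptom scores. Logistic models cover reliable improvement, recovery, reliable recovery and "rates of clients with planned discharges". The only restriction repeated there is SAPAS-SR of 3 or more.

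Table 1 schedules PHQ-9, GAD-7 and WSAS at the first and last session, and SAPAS-SR at the first session or instance. The text after Table 2 says that discharge code and session counts are captured in addition, as measures of engagement.

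**The concern.** A second set of scores exists only if the client stays long enough to give one. Requiring it cuts the distribution of sessions attended from below and removes clients who are unlikely to have a planned discharge. Selection is then on an event after the start of treatment that is closely tied to the outcome.

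Training could change how many clients are removed. Under The intervention, the workshop covers handling the alliance with clients who are ambivalent about help, managing ruptures, and judging who is likely to benefit from care in this setting. The first two could reduce very early exits and the third could increase them. Either way, the excluded share may differ between cohorts because of the training.

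These analyses are exploratory and report no p values. Their effect sizes are nevertheless meant to inform the decision to continue to a definitive evaluation and its power calculation, so a biased estimate has a use to damage.

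**Working it through.** **1. The plan's own client total.** Sample size (service-level data): 120 therapists × 20 clients × 2 periods = 4800, or 2400 per cohort. This reproduces the stated figure.

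**2. Ceiling on how many clients the rule could remove.** With SAPAS-SR of 3 or more in 69% to 81%:
- per cohort: 2400 × 0.69 = 1656 to 2400 × 0.81 = 1944;
- at exactly 60% availability, analysed: 1656 × 0.6 = 994 to 1944 × 0.6 = 1166;
- left out: 1656 × 0.4 = 662 to 1944 × 0.4 = 778.

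This assumes that availability in the subgroup equals availability overall. It is an upper limit at the pass mark: part of the 40% may lack a SAPAS-SR rather than a second score, and those clients could not be classified under any rule.

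**3. What the rule does to the two outcomes (all rates assumed).** Let q be the share of starters with only one score. Assume that they attend 1 session and have no planned discharge. Assume that clients with two or more scores have 60% planned discharge and a mean of 8 sessions in both cohorts. In all starters:
- planned discharge = (1 − q) × 0.60;
- mean sessions = q × 1 + (1 − q) × 8.

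| q before → after | Planned discharge, all starters | OR | Mean sessions, all starters | Difference |
|---|---|---|---|---|
| 10% → 5% | 54% → 57% | 1.13 | 7.30 → 7.65 | +0.35 |
| 20% → 15% | 48% → 51% | 1.13 | 6.60 → 6.95 | +0.35 |
| 30% → 20% | 42% → 48% | 1.27 | 5.90 → 6.60 | +0.70 |
| 40% → 30% | 36% → 42% | 1.29 | 5.20 → 5.90 | +0.70 |
| 20% → 25% | 48% → 45% | 0.89 | 6.60 → 6.25 | −0.35 |

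In the two-score set every row gives 60% v 60% (OR 1.00) and 8 v 8 sessions (difference 0). That zero follows from placing the whole effect in single-score clients.

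**4. The sign can reverse.** Take 20% → 15%, but let the newly retained 5% have only 20% planned discharge.
- All starters: 0.80 × 0.60 = 48.0% → 0.80 × 0.60 + 0.05 × 0.20 = 49.0%.
- Two-score set: 60.0% → 0.490 / 0.85 = 57.6%.

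**5. The 60% rule and the cohorts.** The Table 2 rows on attendance and on attitudinal change are set per site or per service; this row names no split by site or cohort. If it is taken over both cohorts at equal size, 30% before and 90% after gives (0.30 × 2400 + 0.90 × 2400) / 4800 = 2880 / 4800 = 60%, a pass. The split is hypothetical; it shows only that one overall figure need not describe either cohort.

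**The case against.** The strongest reply is that Table 2 defines a feasibility metric, not an analysis set. Clinical outcomes names one restriction, SAPAS-SR of 3 or more, and session counts and discharge codes are introduced as a separate data stream. The authors may intend a wider set for them. That is possible, but the document does not say so. Table 2 and Primary analyses both describe the two-measure condition as governing inclusion, and the engagement models sit inside the evaluation it governs.

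The wording on two measures is also loose. The Discussion notes that low-intensity practitioners often do intake assessments. If scores from intake count, a client with one high-intensity session could have two. The first-and-last schedule in Table 1 favours two treatment occasions but does not settle it. On either reading, those lost are the clients who leave before a second score.

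Several stronger conclusions are tempting and not supported:
- **That the engagement analyses cannot show any effect on retention.** Clients who drop out later with two scores stay in, so their shorter treatment and unplanned discharge remain visible.
- **That training should reduce early drop-out.** The workshop content is compatible with either direction.
- **That SAPAS-SR will be sparse before training.** The eligibility wording, "Services willing to screen for personality difficulties as part of routine assessment will be eligible to participate as a research site", does not show this, and Sample size expects the 69% to 81% prevalence in both cohorts.
- **That SAPAS-SR timing is left open.** Table 1 sets it at the first session or instance.

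Neither engagement outcome appears in a continuation rule, which limits the consequences.

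**Conclusion.** The point holds in a bounded form. As written, one inclusion rule covers all the client analyses, and for sessions attended and planned discharge it selects on an event bound up with the outcome. An effect of training on leaving before a second score would be hidden or distorted.

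Neither size nor direction can be derived from the document. Under the assumed rates, planned-discharge odds ratios of 1.13 to 1.29 and gains of 0.35 to 0.70 sessions in all starters become 1.00 and 0, and a harmful change is concealed in the same way. These figures show the mechanism and do not forecast the bias.

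The conclusion rests on reading Table 2 and Primary analyses as defining who enters the evaluation. The missing cohort split in the 60% rule is a lesser reporting point. The matter is worth correcting before the data are analysed, but it does not undermine the study's main feasibility aims.

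**What to change.** - In Clinical outcomes, state that sessions attended and planned discharge are analysed in all clients with SAPAS-SR of 3 or more who attended at least one high-intensity session, however many outcome scores they have.
- Keep the two-measure requirement for the symptom, functioning, recovery and reliable-change outcomes only.
- Report data completeness for the before and after cohorts separately, alongside the 60% rule.

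The cost is a few sentences. Discharge codes and attendance counts are already to be captured, so no new data collection is needed. The engagement and symptom analyses will have different denominators, which should be shown. The symptom models will still exclude clients without a second score; reporting numbers by cohort makes that visible but does not remove it.

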**Discussion:**

This feasibility study will provide data on the acceptability and feasibility of delivering brief therapist training to adapt usual HICBT to optimise care for individuals with secondary personality difficulties seeking treatment in TTad services for a primary problem of depression and/or anxiety. The study will also evaluate proof of concept that such an approach has the potential to improve clinical outcomes for those with secondary personality difficulties and report any possible harms identified. The study will inform the design of a future randomised controlled trial designed to test the effectiveness and cost-effectiveness of the training.

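### Recovery as written needs a downward crossing on both PHQ-9 and GAD-7, so a client above only one cut-off at intake can never count as recovered

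*Protocol article*

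**What the plan says.** The derived client metrics are in the protocol article under Outcomes, in the paragraph below Table 2. They are introduced with "In line with standard reporting of TTad outcomes" and a citation.

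- Recovery: "as defined by moving ≥ 10 to ≤ 9 on the PHQ-9 and from ≥ 8 to ≤ 7 on the GAD-7".
- Reliable improvement: "improving by ≥ 6 points on the PHQ-9 or ≥ 4 points on the GAD-7".
- Reliable recovery: "as defined by fulfilling criteria for both" recovery and reliable improvement.

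Statistical methods, Clinical outcomes, states how they are used: "Comparable binary logistic regressions will examine binary outcomes (rates of reliable improvement, recovery, and reliable recovery", among others. The predictor is treatment cohort (before or after training), with site as covariate. The population for the clinical analyses is given in the same section: "These analyses will focus solely on the subgroup of participants meeting the criteria for probable personality disorder (3 or more on the SAPAS-SR". Table 2 adds a data requirement of one SAPAS-SR and at least two minimum-dataset measurements. Neither place sets a condition on intake PHQ-9 or GAD-7.

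The Abstract (Discussion) describes the clients as "seeking treatment in TTad services for a primary problem of depression and/or anxiety".

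**The concern.** The recovery sentence sets a start and an end condition on each scale and joins the two scales with *and*. The definition of reliable improvement beside it uses *or*, so the connective appears to carry meaning. Taken at its word, the rule makes caseness on both scales at intake a precondition for recovery. That fits poorly with clients whose primary problem may be depression alone or anxiety alone.

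An analyst who codes from this sentence would score a client with a large fall on the one elevated scale, and both final scores below cut-off, as not recovered. Reliable recovery inherits the problem. Two of the planned binary outcomes would then be lower than intended, and a real difference between cohorts would be diluted by clients whose outcome is fixed in advance. The article intends the between-cohort effect sizes to inform the decision to continue and the power calculation for a randomised trial.

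**Working it through.** **Inputs from the article.** The cut-offs and connectives are quoted above. Sample size (Service-level secondary data sample) gives 120 therapists, more than 20 clients each per 6-month period, and 69% to 81% with SAPAS-SR of 3 or more. Background gives recovery of about 40% in this client group.

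**Step 1, the stated sample.** 120 × 20 × 2 = 4800, which matches the article's figure of more than 4800. Per cohort, 2400 × 0.69 = 1656 and 2400 × 0.81 = 1944 clients would be in the subgroup before missing data.

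**Step 2, what the rule can score as recovered.** Score items 0 to 3, so PHQ-9 runs 0 to 27 and GAD-7 0 to 21. There are 28 × 22 = 616 possible final score pairs, of which 10 × 8 = 80 lie below both cut-offs. The comparison rule is: above at least one cut-off at intake, below both at the end.

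| Intake status | Intake pairs | Start–end combinations | Recovered, as written | Recovered, comparison rule |
|---|---|---|---|---|
| PHQ-9 only | 18 × 8 = 144 | 88,704 | 0 | 144 × 80 = 11,520 |
| GAD-7 only | 10 × 14 = 140 | 86,240 | 0 | 140 × 80 = 11,200 |
| Both | 18 × 14 = 252 | 155,232 | 252 × 80 = 20,160 | 20,160 |
| Neither | 10 × 8 = 80 | 49,280 | 0 | 0 |

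These are counts of score combinations, not probabilities. They show that the two rules differ only for clients above one cut-off, and that for those clients recovery as written is impossible.

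**Step 3, one client.** PHQ-9 18 to 3 is a fall of 15 and GAD-7 7 to 2 a fall of 5. The client is reliably improved on either scale and ends below both cut-offs. GAD-7 never was 8 or more, so the client is not recovered and not reliably recovered.

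**Step 4, size under assumptions.** Let *s* be the share of cases above one cut-off only. The article does not give it; 10% to 30% is assumed. Assume also 40% recovery among all cases by the comparison rule, equal in single-scale and dual-scale clients. The rate as written is then 0.40 × (1 − *s*):

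- *s* = 10%: 0.40 × 0.90 = 36%
- *s* = 20%: 0.40 × 0.80 = 32%
- *s* = 30%: 0.40 × 0.70 = 28%

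Clients below both cut-offs, if kept in, lower it further. With 20% of all clients above one cut-off and 10% above neither, 0.40 × (1 − 0.20 − 0.10) = 28%.

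**Step 5, the cohort contrast.** Take an assumed 40% against 45% among cases. As written the difference is 5 × (1 − *s*) points. The last column is the number per arm for a simple individually randomised comparison of two proportions (two-sided 5%, 80% power, pooled-variance formula).

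| *s* | Rates as written | Difference | Odds ratio | n per arm |
|---|---|---|---|---|
| 0 | 40.0% vs 45.0% | 5.0 | (0.45/0.55)/(0.40/0.60) = 1.23 | 1534 |
| 10% | 36.0% vs 40.5% | 4.5 | (0.405/0.595)/(0.36/0.64) = 1.21 | 1830 |
| 20% | 32.0% vs 36.0% | 4.0 | (0.36/0.64)/(0.32/0.68) = 1.20 | 2201 |
| 30% | 28.0% vs 31.5% | 3.5 | (0.315/0.685)/(0.28/0.72) = 1.18 | 2677 |

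The difference in rates shrinks in proportion to 1 − *s*. The odds ratio, which is what a logistic model estimates, moves less.

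**The case against.** The strongest reply is that the sentence is shorthand. The article says the metrics follow standard service reporting and cites a source, and it says a fuller study protocol can be requested. The intended rule and the denominator may be set out there. This stands in part. The source is not reproduced, so no departure from it is claimed, and no denominator for recovery is stated anywhere in the article. That single-scale and non-case clients count as failures is an inference from the only analysis set given. It does not rescue the sentence: if the intent differs, the text misstates it, and dropping non-cases would still leave single-scale clients unable to recover.

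A second reply is that a primary problem of depression or anxiety is not the same as questionnaire caseness, since a client treated for anxiety may also score 10 or more on PHQ-9. That is right, and is why the single-scale share is left as an assumption.

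A third is that little hangs on the outcome. No continuation rule in Table 2 uses recovery, no p values will be reported, and both cohorts are scored alike. This stands, and it limits the weight of the point.

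Three stronger readings are tempting, and the article does not support them.

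- A reader might infer that the study's rate cannot be compared with the 40%, 50% and 50.2% in the Background. The article does not say how those figures were scored.
- A reader might infer that the rule is inferior because it moves with case-mix. The alternative moves too. If single-scale clients ended below both cut-offs in 51% and dual-scale clients in 28% (assumed), a rise in *s* from 10% to 20% would take the rate as written from 0.90 × 28% = 25.2% to 0.80 × 28% = 22.4%. It would take the alternative from 0.10 × 51% + 0.90 × 28% = 30.3% to 0.20 × 51% + 0.80 × 28% = 32.6%.
- A reader might link the improvement-only metrics to the Abstract's promise to "report any possible harms identified" and call for a deterioration metric. That is a separate preference. The continuous-score models can show average worsening, and Table 2 has a rule on serious negative consequences.

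**Conclusion.** The point holds as a defect in a stated definition. Followed literally, no client above only one cut-off at intake can be recovered or reliably recovered, whatever the final scores. This follows from the wording and needs no assumption beyond reading it as written.

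That these clients, and those below both cut-offs, enter the logistic models as failures is inferred from the stated subgroup and data requirement.

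The size is illustrative: 36% to 28% instead of 40%, for an assumed single-scale share of 10% to 30% and equal recovery in both groups. A firmer estimate of the drop would need intake and final score distributions that the article does not contain. The article also does not say that the later trial would be powered on recovery, so the sample sizes above show direction and order only.

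The consequence is moderate. It should be corrected before data extraction because the effect sizes are meant to inform continuation and future power calculations. It does not threaten the feasibility aims.

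**What to change.** Replace the recovery sentence with one that states the intake condition, the end condition and the denominator:

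- Intake: PHQ-9 of 10 or more, or GAD-7 of 8 or more.
- Last session: PHQ-9 of 9 or less and GAD-7 of 7 or less.
- Denominator: recovery and reliable recovery are fitted only in clients with SAPAS-SR of 3 or more and sufficient data who meet the intake condition. Report how many are excluded in each cohort.

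Reliable recovery can stay as recovery plus reliable improvement, and then inherits the corrected rule. If the sponsor does intend caseness on both scales, the article should say so and restrict the denominator to clients who meet it.

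The cost is one sentence and one filter, with no new data. The downside is that clients below both cut-offs at intake leave these two models. They remain in the continuous-score, reliable improvement and discharge analyses.
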